## Abstract

**Background:**

At present, scientific consensus exists on the multifactorial etiopatogenia of obesity. Both professionals and researchers agree that treatment must also have a multifactorial approach, including diet, physical activity, pharmacology and/or surgical treatment. These two last ones should be reserved for those cases of morbid obesities or in case of failure of the previous ones. The aim of the PRONAF study is to determine what type of exercise combined with caloric restriction is the most appropriate to be included in overweigth and obesity intervention programs, and the aim of this paper is to describe the design and the evaluation methods used to carry out the PRONAF study.

**Methods/design:**

One-hundred nineteen overweight (46 males) and 120 obese (61 males) subjects aged 18–50 years were randomly assigned to a strength training group, an endurance training group, a combined strength + endurance training group or a diet and physical activity recommendations group. The intervention period was 22 weeks (in all cases 3 times/wk of training for 22 weeks and 2 weeks for pre and post evaluation). All subjects followed a hypocaloric diet (25-30% less energy intake than the daily energy expenditure estimated by accelerometry). 29–34% of the total energy intake came from fat, 14–20% from protein, and 50–55% from carbohydrates. The mayor outcome variables assesed were, biochemical and inflamatory markers, body composition, energy balance, physical fitness, nutritional habits, genetic profile and quality of life. 180 (75.3%) subjects finished the study, with a dropout rate of 24.7%. Dropout reasons included: personal reasons 17 (28.8%), low adherence to exercise 3 (5.1%), low adherence to diet 6 (10.2%), job change 6 (10.2%), and lost interest 27 (45.8%).

**Discussion:**

Feasibility of the study has been proven, with a low dropout rate which corresponds to the estimated sample size. Transfer of knowledge is foreseen as a spin-off, in order that overweight and obese subjects can benefit from the results. The aim is to transfer it to sports centres. Effectiveness on individual health-related parameter in order to determine the most effective training programme will be analysed in forthcoming publications.

**Trial registration:**

ClinicalTrials.gov NCT01116856

## Background

The increase in overweight and obesity rates is a major public health concern. In most countries it has affected all population groups regardless of sex, age, race, income or education level, but to varying extents [1]. Based on comparative studies with other European countries, Spain is at the forefront [1], one in four people is overweight or obese, ie 12.5 million people [2]. In fact, two out of three men are overweight and one of every six is obese, with a clear trend to increase in the forthcoming years [3].

Today it is accepted that obesity has a multifactorial origin [4,5] and is a known risk factor for numerous health problems, including high cholesterol, diabetes, hypertension, respiratory problems, musculoskeletal diseases, cardiovascular diseases, and some forms of cancer. Mortality also increases sharply once the overweight threshold is crossed [6,7].

Research has been very active in the last years trying to identify the most effective treatment for adult overweight and obesity [8-40]. A combination of caloric restriction with an increase in energy output by means of exercise has been proven in the hospital setting [41]. Results have been quite conclusive regarding aerobic exercise [9] and very restrictive caloric intake (less than 50% of kcal intake) [35]. But data are still scarce regarding the effect of a combination of strength and aerobic training and a much lesser restrictive hypocaloric diet on weight loss [35]. The PRONAF study wants to get deeper into the latter, also considering the Consensus Paper 2011 from the Spanish Society of Obesity Research (SEEDO), that has stated that the primary goal of treatment should not focus on achieving the ideal body weight, but to have smaller weight losses maintained in the long term [42].

Therefore, the main aim of the PRONAF study was to discover which is the most effective training protocol in combination with caloric restriction for overweight and obese subjects included in a specific intervention program. The aim of this paper is to describe the design and the evaluation methods used for the PRONAF study.

## Methods/design

### Study design

PRONAF is a 22 week-intervention study performed among Spanish overweight and obese adults, who were randomly assigned to one of the following intervention groups: strength training group (S), endurance training group (E), combined strength plus endurance training group (SE), and physical activity recommendations group (C), which are described in detail below. The study was performed twice, one year apart, first in the overweight group (year 2009/2010) and then in the obese group (year 2010/2011). In total, we had 8 interventions groups.

### Population and sample size estimation

The estimation of the sample size was calculated to detect a main effect of the treatment on the percentage of body fat with a 80% statistical power at 5% significance, assuming a 0.80 correlation between repeated measures [43]. The initial calculated sample size per intervention group (n = 22) permits the detection of a large effect size (Cohen’s d = −0.8), as observed in a previous investigation [43].

The initial adjustment of sample size for dropouts carried out used a maximum of 25% of dropouts in each group [37]. Adjusted dropouts sample = n (1/1-R), where n = number of subjects not lost, and R = expected proportion for dropouts. With our data, the initial necessary sample size was: 88 (1 / 1–0.25) = 118 subjects or 29/30 in each intervention group, this being applicable for both the overweight and the obese interventions groups. A total of two hundred thirty nine people initiated the study, completing it 180 (75.3%), which supposed 59 dropouts for different reasons. For personal reasons 17 (28.8%), low exercise adherence 3 (5.1%), low diet adherence 6 (10.2%), job change 6 (10.2%), and lost interest 27 (45.8%).

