### Statistical analysis

The main independent variables of the study were: intervention group, age, gender, measurement (baseline – post) and BMI classification (overweight or obese). The delta percentage was calculated thought the standard formula: change (%) = [(post-test score − pre-test score)/pre-test score]*100. The power calculated previously to find significant differences between groups was 0.8 to fat mass (%).

Standard statistical methods will be used for the calculation of the means and standard deviation for all dependent variables. The statistical analysis will be as follows: 1) Univariate descriptive analysis, study of data distribution, basic statistics such as central and dispersion values. Pair comparison tests with previous analysis of the homogeneity of variance will be used. Pearson correlation coefficients, chi-squared tests and exact probability calculations will be also performed to study the relationship between quantitative and qualitative variables, respectively; 2) General lineal models, such a multivariate analysis (MANOVA) or two way analysis of variance (ANOVA) for repeated measures, will be used to determine differences among the four interventions groups and between baseline and post-training values. Compound symmetry, or sphericity, will be verified by the Mauchly test. When the assumption of sphericity would not be met, the significance of F ratios will be adjusted according to the Greenhouse-Geisser procedure. Multiple comparisons of ANOVAs will be made with the Bonferroni post -hoc test.

The analysis of the data will be done using statistical package SPSS (SPSS Inc., Chicago, Illinois, USA). The significant level will be set at α = 0.05.

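### The stated 80% power matches a group effect averaged over baseline and post at an unadjusted 5% level, and is not the power of the Bonferroni between-arm comparisons the plan describes

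*Protocol article*

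**What the plan says.** Under Population and sample size estimation, the protocol article states that the size was set to "detect a main effect of the treatment on the percentage of body fat with a 80% statistical power at 5% significance", assuming a correlation of 0.80 between repeated measures. It continues: "The initial calculated sample size per intervention group (n = 22) permits the detection of a large effect size", with Cohen's d given as −0.8. The four arms make 88, raised to 118 for 25% dropout, and this number is applied to the overweight and the obese cohort separately.

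Under Statistical analysis, the figure returns as a general statement: "The power calculated previously to find significant differences between groups was 0.8 to fat mass" (in per cent). The planned model is a MANOVA or a two-way repeated-measures ANOVA over four groups and two time points. Then: "Multiple comparisons of ANOVAs will be made with the Bonferroni post -hoc test". The level is fixed in the same section: "The significant level will be set at α = 0.05".

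The Background gives the main aim as finding which training programme works best, which requires comparing arms with one another. The time line places the first of the two assessments one week before the intervention.

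**The concern.** Three things do not line up.

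- **The effect.** The calculation names a main effect of treatment. In a group-by-time layout with one measurement before and one after, the group main effect is the arm difference averaged over both occasions. Randomised arms have equal expected values at baseline, so half of that average carries no treatment effect. The informative contrast is the difference in change (group × time) or the baseline-adjusted post value.
- **The level.** The size uses 5% unadjusted, while the comparisons among arms are to be Bonferroni-corrected.
- **The unit.** The article does not say whether d = −0.8 is in SDs of percentage body fat or SDs of its change. With a correlation of 0.80 the two differ greatly.

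At stake is how the coming effectiveness papers are read. The Discussion counts meeting the sample size estimate as a strength, and the 80% is the only guide a reader has to how much a non-significant difference between arms tells.

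**Working it through.** **Inputs from the protocol article:** d = 0.8, r = 0.80, power 80%, alpha 0.05, n = 22 per arm, four arms. Two-sided testing is assumed, since sidedness is not stated.

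**Step 1. Reproduce 22.** Two-group formula: n = 2 × (1.960 + 0.842)² × V / d², where V is the variance factor. With V = 1 this is 24.53 per arm.

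| Quantity tested | V | n per arm (normal) | n per arm (t) |
|---|---|---|---|
| Single measurement, r ignored | 1 | 24.53 → 25 | 26 |
| Mean of baseline and post | (1 + 0.8)/2 = 0.90 | 22.07 | 24 |
| Change score, d in raw SDs | 2(1 − 0.8) = 0.40 | 9.81 → 10 | 11 |
| Baseline-adjusted post, d in raw SDs | 1 − 0.8² = 0.36 | 8.83 → 9 | 10 |

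The averaged version at n = 22 has 79.9% power by the normal approximation and 78.0% by t. A four-arm F-test on the same average, with one arm differing by 0.8, has f = 0.8 × √3/4 = 0.346 and f²/0.90 = 0.133. Its power is 79.0% at 21 per arm and 81.2% at 22, so 22 is the smallest size that reaches 80%. A one-sided test on one measurement gives 20–21 but makes no use of the stated correlation. The match with the average is therefore close, but it is an inference.

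**Step 2. Put baseline before the intervention.** Expected difference in the average: (0 + 0.8)/2 = 0.4 raw SD. SD of the average: √0.90 = 0.949. Standardised effect: 0.4/0.949 = 0.42. Power at 22 per arm is 28% for two groups (90 per arm needed for 80%) and 26% for the four-arm F-test with one arm differing.

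**Step 3. Power of the Bonferroni comparisons.** Four arms give six pairs, so alpha = 0.05/6 = 0.0083; three comparisons with the recommendations group give 0.05/3 = 0.0167. The ranges below come from noncentral t at n = 22 per arm, with 42 error df (two arms) or 84 (all four arms).

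| Contrast | Standardised effect | alpha 0.05 | 0.05/6 | 0.05/3 |
|---|---|---|---|---|
| Averaged effect as sized (difference at both times) | 0.8/√0.90 = 0.84 | 78–79% | 52–54% | 62–64% |
| Change, d in SDs of change | 0.80 | 74–75% | 46–48% | 57–58% |
| Change, d in raw SDs, r = 0.80 | 0.8/√0.40 = 1.26 | 98–99% | 92–93% | 95–96% |

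No entry in the two Bonferroni columns is close to 80%. For six pairs, the difference detectable with 80% power at 22 per arm is 1.10 SDs of the tested quantity (1.07 with 84 df). With d in SDs of change, 39–40 per arm would be needed.

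**Step 4. Cohorts pooled.** There are 180 completers, so 180/4 = 45 per arm if balanced. With d = 0.8 in SDs of change and alpha 0.05/6, power is 86% (two-arm df).

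**The case against.** The strongest reply has four parts.

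- **No formula is printed.** The words main effect may simply mean treatment effect, and the two-group version gives 22.07, which strictly rounds up to 23. This stands as a limit: the averaging is inferred from the wording, the use of r and the numerical match. The four-arm F-test version also yields 22, but it averages baseline and post too, so the dilution remains.
- **The plan does not commit to testing the averaged effect.** A two-way repeated-measures ANOVA contains the group × time test, and the article also defines percentage change. This stands. The 26–28% describes the effect named in the sizing statement; it does not predict how the trial will be analysed.
- **Sizing on an overall test at 5% and then using corrected post-hoc pairs is common, and the article nowhere claims 80% for each corrected pair.** This stands as to the wording. But an overall test does not say which programme is best, and the analysis section gives 0.8 for differences between groups without saying which test it means.
- **The cohorts may be pooled.** BMI class is listed as an independent variable, and pooling brings even the unfavourable case to 86%. That is fair, but the size is set for each cohort separately, and the article does not say to which analysis the 80% belongs.

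A reader might infer that the trial is underpowered. The documents do not support that: if d is in raw SDs, the corrected pairwise power for change is above 90% within a single cohort. Nor do they say that non-significant differences will be read as equivalence.

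**Conclusion.** The point holds as a mismatch between the stated power and the planned comparisons. With the printed inputs, 22 per arm fits a group effect averaged over baseline and post at an unadjusted 5%. For a difference that arises only after randomisation, that effect has about 26–28% power. For the between-arm difference in change within one cohort, with six Bonferroni pairs, power is about 46–48% or 92–93% according to the SD behind d; for three comparisons it is 57–58% or 95–96%.

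This rests on two-sided tests, 22 completers per arm, r = 0.80 and the inferred formula. The Bonferroni mismatch does not depend on that inference: even the averaged effect exactly as sized has only 52–54% power at 0.05/6. The direction of the error cannot be settled from the article. The sum 88/0.75 = 118 (rounded up) is correct.

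**What to change.** In Population and sample size estimation and in Statistical analysis:

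1. Name the powered contrast as the between-arm difference in change in percentage body fat. This can be the group × time term, already within the planned repeated-measures ANOVA, or the baseline-adjusted post value.
2. State the SD on which d = 0.8 is defined.
3. Give the number of comparisons, and the power and minimum detectable difference at the resulting Bonferroni level (for six pairs at 22 per arm, 1.10 SDs of the tested quantity).
4. Say whether the figure applies to each cohort or to both pooled (about 45 completers per arm if balanced).

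No extra participants and no change to the model are needed. The only cost is a restated figure that may be less favourable than 80%, namely if d is in SDs of change and the cohorts are analysed separately.

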### Recruitment of the subjects

Subjects were recruited by means of diverse advertisements published in the media and the applicants filtered using different criteria. The voluntary subjects who fulfilled the inclusion criteria and passed the baseline physical examination were stratified by age ranges and body mass index (BMI), and randomized into the different intervention groups (Figure 1).

**Figure 1 F1:**
[figure not shown]
**Participant flow diagram.** S, strength training group; E, endurance training group; SE, combined strength plus endurance training group; C, physical activity recommendations group.

### Inclusion and exclusion criteria

Inclusion criteria included being male or female living in the Region of Madrid, being overweight (BMI 25–29.9 kg/m^2^) or obese (BMI: 30–34.9 kg/m^2^), middle-aged (from 18 to 50 years), having a sedentary lifestyles (< 30 min Physical Activity/day), being normoglycaemic, and non-smoker [37,41]. In the case of females, having regular menstrual cycles was required.

The exclusion criteria were suffering from a physical (orthopaedic limitations, stroke, etc.) and/or psychological (anorexia, bulimia, etc.) disease that may have precluded the performance of the requested strength or endurance training, intake of any medication (beta blockers, alcohol, etc.) known to influence physical performance or the interpretation of the results, having a history of systematic strength or endurance training (moderate to high intensity training more than once a week) in the year before the beginning of the study [37,40].

After the intervention period, participants who failed to comply with 90% assistance to the training sessions and less than 80% adherence to the diet were excluded from further analysis. The characteristics of the final sample (completers) are shown in Table 1.

**Table 1 T1:** Baseline data (n = 180)

	**Overweight n = 84**		**Obesity n = 96**	
	**Women**	**Men**	**Women**	**Men**
	**n = 48**	**n = 36**	**n = 48**	**n = 48**
Age (years)	37.29 ± 8.25	37.42 ± 8.02	39.02 ± 7.74	38.79 ± 7.99
Body Weight (kg)	73.5 ± 5.87	88.21 ± 8.13	88.33 ± 10.1	102.04 ± 8.94
Height (m)	1.62 ± 0.06	1.75 ± 0.07	1.64 ± 0.07	1.77 ± 0.06
BMI (kg/m^2^)	28.01 ± 1.32	28.57 ± 1.12	32.41 ± 1.85	32.4 ± 1.9
Body fat (%)	43.28 ± 3.62	33.8 ± 4.63	47.11 ± 3.49	38.17 ± 4.02
Body fat free mass (kg)	40.25 ± 4.3	55.99 ± 5.47	44.3 ± 4.71	58.63 ± 8.96
Bone mineral density (g/cm^2^)	1.18 ± 0.1	1.26 ± 0.09	1.21 ± 0.11	1.3 ± 0.1

Results are shown as Mean ± SD.

*Note*. BMI = Body Mass Index. Body fat, Body fat free mass and Bone mineral density calculated by Dual-energy x-ray absorptiometry (DXA).

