#### Exercise protocols

Four different intervention groups were involved in the study as stated above. The S, E and SE groups followed the corresponding training program plus the dietary intervention, and the C group followed the dietary intervention and was instructed about the general recommendations regarding physical activity for weight loss from the American College of Sports Medicine (ACSM) [44].

Subjects in the S, E and SE groups performed training 3 times/wk for 22 weeks at a Sports Centre in Madrid (Spain). All training sessions were carefully supervised by certified personal trainers. The exercise programs were designed taking into account each subject’s muscle strength (MS) and the heart rate reserve (HRR). MS was measured using the 15-repetition maximum (15 RM) testing method [45] in the S and SE groups (both of which involved strength training). Both volume and intensity of exercise was increased over the study period (Figure 2) according to standard procedures [35,41].

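### Participants are excluded after randomisation for low attendance or diet adherence, so the analysis of 180 of 239 no longer compares the randomised groups and may be biased in an unknown direction

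*Protocol article*

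**What the plan says.** The exclusion rule stands in the protocol article under Inclusion and exclusion criteria. It applies after the intervention: "participants who failed to comply with 90% assistance to the training sessions and less than 80% adherence to the diet were excluded from further analysis". What remains is defined in the next sentence: "The characteristics of the final sample (completers) are shown in Table 1". Table 1 has n = 180.

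The Abstract gives the randomised numbers: "One-hundred nineteen overweight (46 males) and 120 obese (61 males) subjects aged 18–50 years were randomly assigned". Population and sample size estimation gives the flow: "A total of two hundred thirty nine people initiated the study, completing it 180 (75.3%), which supposed 59 dropouts for different reasons". The reasons listed are personal 17, low exercise adherence 3, low diet adherence 6, job change 6 and lost interest 27.

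Exercise protocols describes supervised sessions three times a week for 22 weeks in S, E and SE. For the fourth arm it says that "the C group followed the dietary intervention and was instructed about the general recommendations regarding physical activity"; no supervised sessions are described for C. The section on energy balance and adherence defines exercise adherence as sessions performed over total sessions, and diet adherence as prescribed energy over actual intake, each times 100.

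Statistical analysis plans repeated-measures ANOVA or MANOVA on baseline and post values. It describes no analysis of all randomised participants. The Discussion counts the retained final sample as a strength and reports that the groups did not differ in number of dropouts.

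**The concern.** Randomisation makes the arms comparable at baseline. A filter applied 22 weeks later on behaviour that the arm itself can influence does not preserve this. Those who stay in one arm need not be the same kind of people as those who stay in another.

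The main aim is to find which training type works best with caloric restriction, for use in intervention programmes. An analysis restricted to adherent completers answers a narrower question, namely what happens in people who attend nearly every session and keep to the diet. It cannot show that an arm performs poorly because people do not sustain it, and its contrasts between arms lack the protection of randomisation.

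**Working it through.** **1. The article's own counts.** 88/(1 − 0.25) = 117.3, rounded up to 118 per BMI cohort, as stated. Randomised: 119 + 120 = 239. Lost: 239 − 180 = 59, and 59/239 = 24.7%. The reasons add up: 17 + 3 + 6 + 6 + 27 = 59. The number who completed (180) equals the number in Table 1, so anyone removed under the adherence rule is already among the 59.

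**2. Where the losses fall.**

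| Stratum | Randomised | Table 1 | Lost |
|---|---|---|---|
| Overweight | 119 | 84 | 35 (29.4%) |
| – women | 73 | 48 | 25 (34.2%) |
| – men | 46 | 36 | 10 (21.7%) |
| Obese | 120 | 96 | 24 (20.0%) |
| – women | 59 | 48 | 11 (18.6%) |
| – men | 61 | 48 | 13 (21.3%) |

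These are descriptive. The text gives no losses by arm, and the flow diagram is not shown in the copy reviewed.

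**3. Losses attributed to adherence.** 3 + 6 = 9, which is 9/59 = 15.3% of losses and 9/239 = 3.8% of those randomised. The remaining 50 have other stated reasons.

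**4. What the two filters select on.**
- Attendance: 3 × 22 = 66 sessions. 60/66 = 90.9% passes and 59/66 = 89.4% fails, so a seventh missed session removes a participant. This can happen only in S, E and SE.
- Diet: prescribed/actual < 0.80 means actual intake above 1/0.80 = 125% of that prescribed. The rule sets no limit in the other direction, so it drops those who overate and keeps those who restricted more than asked. That is selection on a determinant of fat loss, and body fat percentage is the variable on which the trial is sized.

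**5. How far could an arm mean move?** The documents give no outcomes for those removed, so these are bounds under assumptions, not estimates. If outcomes are normal and the fraction p removed are exactly the worst responders, the retained mean shifts by φ(z_p)/(1 − p) SD.
- The 3 attendance losses, training arms pooled: equal allocation gives about 239 × 3/4 = 179, p = 1.7%, shift 0.04 SD. If all three were in one of the eight groups (239/8 = 29.9, p = 10%), the bound for that group is 0.20 SD.
- All 9 adherence losses in the pooled training arms: p = 5%, shift 0.11 SD.
- All losses, p = 24.7%: 0.42 SD, or 0.21 SD if the tendency to be lost and response correlate at 0.5.

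Each figure is a shift in a mean on one side of a comparison. It carries over to a contrast only if the other side has no such selection; similar selection on both sides largely cancels.

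Nor do these figures compare directly with the design effect of d = 0.8, because the article does not say on which SD scale d is defined. A two-sided calculation for a group effect averaged over both time points gives 2 × 0.9 × ((1.960 + 0.842)/0.8)² = 22.07 per group. This is close to the stated 22 and implies raw-score SD units. With the stated correlation of 0.80, the SD of change is √(2 × 0.2) = 0.632 raw SD. If the shifts are in SD of change, 0.419 becomes 0.265 and 0.21 becomes 0.133 raw SD.

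**6. Direction.** The attendance filter alone would favour training over C if poor attenders respond worse. The diet filter can act in all four arms, and the other 50 losses have no arm in the text, so the net sign is undetermined. Among S, E and SE the attendance rule is the same, and no favoured arm follows.

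**The case against.** The strongest defence has four parts.

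First, this is a condensed article, and a fuller plan may hold an as-randomised analysis. That would excuse silence, but the article is not silent: it states the exclusion and names the remaining set as the final sample.

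Second, few losses are attributed to adherence. This stands: 9 of 239, of which only 3 concern attendance. Most of the 24.7% is ordinary attrition, and the rule should not be charged with it. Attrition after randomisation still needs a method, however, and a completer analysis supplies none.

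Third, the groups did not differ in number of dropouts. This is relevant and makes a gross imbalance less likely. It says nothing about who left: equal counts with different reasons can still leave different kinds of people in each arm.

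Fourth, the sample was inflated for 25% dropout. That protects precision among completers and does nothing about selection.

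A reader might go further and infer that the comparison is biased towards the supervised training arms, because only they face the attendance test. The documents do not support this, for the reasons in step 6 of the working. A reader might also infer that a completer effect is overstated by a third (1/0.75 = 1.33). That requires those lost to have had no benefit at all, which nothing in the article shows.

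**Conclusion.** The concern holds as a defect of the analysis set. Both criteria are measured after randomisation and can depend on the arm, one of them cannot operate in C, and no analysis of all randomised participants is described. The planned comparison is therefore not a comparison of the randomised groups and may be biased. What is certain is the extent of the missing group: 59 of 239, with 9 attributed to low adherence. The direction and size of any bias cannot be determined from the text; the bounds in the working rest on normality, worst-case selection and assumptions about allocation.

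The rule is also ambiguous. It joins the criteria with the word and, which taken literally requires both failures and leaves its application to C undefined. The separate exercise and diet counts suggest that either failure sufficed. The conclusion does not depend on which reading is right, since both select on behaviour after randomisation.

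**What to change.** - Define the primary analysis as all 239 participants in their assigned arm, using every available week-22 value regardless of attendance or diet adherence.
- Handle missing week-22 values with a mixed model or multiple imputation based on baseline values, age, sex and BMI. If the 15-day body weights are used as well, allow for group C having weighed themselves on their own scales at home (Body weight control), while the others were weighed at the Sports Centre.
- Keep the 90%/80% set as a secondary analysis labelled per-protocol.
- Report exclusions and losses by arm and reason.
- State whether the two criteria are joined by and or by or.

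Cost: revised analysis wording and one additional analysis. Effectiveness results are deferred to later publications, so the change can still be made. The article does not show that week-22 values exist for those who left, so much of the added information may come from the missing-data model and depend on its assumptions. The estimate may be smaller and its interval wider.

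The planned 118 per cohort is unchanged if d = 0.8 is kept for all randomised. As an assumed range, if the 24.7% lost had half the effect, d is 0.70 and power at 29.9 per arm is 0.82. If they had none, d is 0.60 and power is 0.69. Both use the formula that gives 22.07 and treat every outcome as observed, so they are on the favourable side.
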